3. CDSS

The CDSS consists of a flag which appears on the EHR whenever a patient on the at-risk asthma register makes contact with any member of the practice team and the clinical record is opened, and is designed to prompt actions as per the practice’s ‘action plan’ (see above). The nature of the flag is dependent on the software used to manage the practice’s EHRs and varies between pop-ups that actively need clearing from screen to yellow Post-it style notes remaining on screen. ARRISA is compatible with the Vision (In Practice Systems Ltd., London, UK), EMIS (EMIS Health, Leeds, UK) and SystmOne (The Phoenix Partnership (TPP), Leeds, UK) EHRs which account for more than 90% of primary care practices in the UK. The wording of the flag is chosen by the practice during the second training module but suggested wording of ‘At-Risk Asthma Prioritise Care’ is given. Instructions for generating the flag are provided to the practice manager/IT lead. The flagging goes live after the completion of the minimum training as defined below

4. Practice support

The practice champion receives a phone call approximately 4 weeks (between 2 and 6 weeks) after the activation of the flags to ensure that there are no technical or other fundamental implementation issues. Practice representatives receive emails containing links to brief videos at 6 weeks and 6 months that remind practices of the purpose of the study and the importance of targeting, prioritising access for, engaging with, and effectively managing, patients with at-risk asthma at every opportunity.

Study newsletters will be circulated to practice representatives for the duration of the study. These provide updates on study progress including number of recruited sites, timelines, etc. In addition, practice staff have access to a helpline manned by an un-blinded IT technician for help with technical issues regarding the software for the duration of the study. The eLearning website contains links to national guidelines and other resources.

Full practice engagement with the training is encouraged as the flag is only activated after the completion of minimum training, which we define as at least one practice member completing both eLearning training modules. If required, we will send reminders to all practice representatives by email on two occasions then contact them by phone to encourage completion of the training. Assessment of engagement with the intervention will form part of the process evaluation and include examination of modifications to the register, uptake and completion of the training and engagement with follow-up phone calls.

### Control

Control practices produce an anonymised list of patients who meet the definition of at-risk asthma from the algorithm. They are given instructions and asked to enter a research-relevant Read code onto patients’ EHRs so that they can be identified for the purpose of data collection. However, practice staff are blind to the names and details of the patients on the list until the end of the study. The practice representatives from the control practices will also receive study newsletters for the duration of the study.

The control practices continue to provide their usual care. This may vary between practices, but reflects the recommendations of the BTS/SIGN British Asthma Guideline [7] and NICE guidelines [25]. Primary care practices in England and Wales are incentivised to provide care to BTS/SIGN standards as defined by the Quality and Outcome Framework (QOF) [27]. This recommends creating a register of all patients with asthma and offering at least annual practice-based asthma reviews (typically in nurse-led clinics). Recognised management includes checking control of asthma symptoms with the Royal College of Physicians’ three questions (RCP3Qs; i.e. difficulty sleeping, daytime symptoms, interference with usual activities), checking smoking status and offering cessation advice, assessing/teaching inhaler technique, assessing and offering advice on adherence, and delivering patient self-management education which may include provision of action plans and self-monitoring tools [28]. Follow-up in secondary care outpatient clinics and use of emergency primary and care services is available as usual for patients, if required.

After completion of the trial, control practice staff will be permitted to undertake the eLearning training and un-blind and modify the register in the same way as intervention practices could at the beginning of the study.

### Outcomes

#### Primary outcome

The percentage of at-risk patients with an asthma-related (defined as asthma, mixed asthma/chronic obstructive pulmonary disease (COPD) and/or mixed asthma/respiratory infections) crisis event – i.e. an A&E attendance, hospitalisation or death – over 12 months.

#### Secondary outcomes

The time to first, and rate of, asthma-related crisis event(s) (defined as above) for at-risk patientsThe percentage of all registered asthma patients with an asthma-related crisis event, their rate of, and time to, first asthma-related crisis event(s) (as above)The percentage of at-risk and all registered asthma patients with good control defined as answering ‘no’ to all of the RCP3Qs [29]The percentage of at-risk and all registered asthma patients requiring a hospital admission or dying for any reasonThe number of the following (per patient per year) for both at-risk and all registered asthma patients:

(a) short-acting bronchodilator prescriptions issued

(b) prescriptions of systemic corticosteroids for asthma attacks and antibiotic-treated lower respiratory tract infections

(c) modifications of the prescription of asthma-related medications to align more closely with current guidelines (e.g. increased use of inhaled corticosteroids)

(d) records of written personalised asthma action plans and patient self-monitoring with peak flow diaries

(e) inhaler technique assessments recorded

(f) smoking cessation advice or smoking cessation medications given

(g) flu vaccinations

(h) ‘did not attends’ at primary and secondary care routine appointments

(i) adherence to medication determined from validated computer-based calculations using prescription data

Health economic outcomes6.The estimated (per patient) mean incremental cost of the at-risk register compared with usual care7.The incremental effect of the at-risk register, in terms of the estimated (per patient) mean difference (between arms) in the number of asthma crisis events

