It is widely accepted that the majority of deaths and hospital admissions from asthma are associated with preventable factors [9]. In 2012, this prompted a National Review of Asthma Deaths (NRAD) [10], which showed that poor access to care and poor adherence with preventive medication(s) were key contributors in the deaths of a large proportion of patients. Patient-assessed poor access to primary care is also associated with emergency hospital admissions for asthma [11]. Unfortunately, due to complicating clinical and psychosocial characteristics, patients with asthma who are at particular risk of attacks (at-risk asthma) often fail to attend routine appointments or engage in initiatives [12], such as self-management education, that improve outcomes in general asthma populations [13]. In addition, these patients characteristically under-use primary care services, often fail to attend scheduled appointments [14, 15] and have difficulty adhering to treatments [16, 17]. It is these same patient groups that are also most often excluded from clinical trials. Existing evidence is thus unlikely to be generalisable [18] and research is urgently needed to identify better management strategies for this group. Systematic nationwide training and implementation programmes, mostly based in primary care, are able to reduce the morbidity and impact of asthma with reduced costs [19]. Also, a clinical care pathway for children with asthma has been shown to modify practice behaviour and reduce emergency department attendance and hospitalisations, but not significantly so, compared to usual care [20]. Indeed, the current British Thoracic Society/Scottish Intercollegiate Guideline Network (BTS/SIGN) British guideline on the management of asthma notes that ‘*well-conducted studies are needed to define the benefits of care pathways for asthma. These should include large, suitably powered studies to clarify the impact of pathways promoting systematic management of people with high-risk asthma in UK primary care’.* [7]

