**Fig. 2 Fig2:**
[figure not shown]
ARRISA-UK schedule of enrolment, interventions and assessments

Routinely available data from patient records on outcomes, processes of care and healthcare use will be captured anonymously, without the involvement of the practice, at the end of the 12-month study period. Additional resource use data, for the purposes of economic evaluation, will be captured during the online training, post training and 12-month questionnaires. Data from a baseline practice demographic survey, the training software, questionnaires completed post training and at 12 months, plus focus groups and individual interviews undertaken with a sub-sample of practice staff and patients towards the end of the study, including those from the whole asthma population and those with at-risk asthma in the intervention and control groups (see below), will contribute to the process evaluation. This will take a mixed-methods sequential explanatory approach to exploring implementation, mechanisms and contextual influences on the intervention.

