### Data collection

#### Baseline characteristics and outcome data

All practices expressing interest in the study are asked to complete an initial questionnaire to provide basic data on practice characteristics.

All participating practices must agree to share their practice EHRs with Optimum Patient Care (Cambridge, UK). Obtaining data in this way not only permits linkage to different databases (practice EHRs, Office for National Statistics (ONS), Hospital Episode Statistics (HES)), but also permits data capture without burdening the practice or patients. All practices (control and intervention) are asked to insert a specific Read code that cannot be readily removed by practice staff into the EHRs of at-risk asthma patients to denote inclusion in this study. This will be used by data managers and statisticians to identify these patients and distinguish their data from other patients with active asthma in the practice. For the purposes of data collection, active asthma is defined using the QOF criterion [27]: Read code for asthma diagnosis plus asthma therapy in the past year, excluding those coded as asthma resolved but not excluding QOF exception codes. At the end of the study, data extractions will be obtained for all patients with asthma in the practice containing data for the 12 months before randomisation and the 12 months following the activation of the flag in the intervention practices. The mean time from randomisation to activation of the flag will be calculated for all intervention practices, and data collection will be captured for 12 months from this time after randomisation in the control practices. For clinical event data and for patients’ demographic and other characteristics (weight, height, smoking status, etc.) the last recorded value will be obtained.

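### Good asthma control is defined over all patients but can be seen only where routine care recorded the RCP3Qs, so a recording gap between arms can pass for a difference in control

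*Protocol article*

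**What the plan says.** All places are in the protocol article.

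- **Secondary outcomes** defines the outcome as the "percentage of at-risk and all registered asthma patients with good control defined as answering" no to all three RCP3Qs. It does not restrict this to patients who have an answer on record.
- **Trial design** (text after the Fig. 2 caption) gives the source: "Routinely available data from patient records on outcomes, processes of care and healthcare use will be captured anonymously, without the involvement of the practice". No RCP3Q administered by the trial is described.
- **Control** describes usual care under the Quality and Outcomes Framework: "This recommends creating a register of all patients with asthma and offering at least annual practice-based asthma reviews". It continues: "Recognised management includes checking control of asthma symptoms with the Royal College of Physicians’ three questions". The same section keeps control staff blind to which patients are on the list.
- **Background** says that at-risk patients "often fail to attend routine appointments or engage in initiatives".
- **Intervention** describes a flag shown when an at-risk patient's record is opened, and reminder videos that stress access and engagement.
- **Baseline characteristics and outcome data** has the extract cover the 12 months before randomisation and the 12 months after flag activation (a matched period in control practices). For clinical event data and patient characteristics, "the last recorded value will be obtained".
- **Effectiveness analyses** assigns logistic regression to binary secondary outcomes.

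**The concern.** The numerator and the denominator rest on different information. Every at-risk patient (or every registered asthma patient) is in the denominator. A patient can enter the numerator only if somebody asked the three questions and recorded the replies. Read literally, a patient who was never asked cannot count as well controlled.

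This would matter little if recording were equal in the two arms. Here the intervention is meant to increase contact with a group that tends to miss appointments, and it does so in one arm only. More contact gives more chances to record the answers, so recording is itself a plausible effect of the intervention.

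The consequence is an arm difference that mixes being asked with being well. Asthma control is the only symptom-based outcome on the list. It is also named as an outcome in the process evaluation, including its regression models, so an artefact could carry over into the explanation of how the intervention works.

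**Working it through.** **The plan's own figure.** The article gives no figure for the RCP3Q outcome. Its sample size reproduces: 7% v 5%, 90% power, two-sided 5% (assumed, not stated) and continuity correction give 3061 per arm. Then 2 × 3061 × [1 + (35 − 1) × 0.01] = 6122 × 1.34 = 8203.5, that is 8204, and 8204 / 35 = 234.4, that is 235 practices. The present point leaves this unchanged.

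**Inputs.** From Sample size and Randomisation: 10,530 patients in 270 practices, 39 per practice, 1:1, so 5265 per arm; ICC 0.01, given for the primary outcome. Assumed: the proportion with an RCP3Q recorded (r0 control, r1 intervention), good control among those recorded (g, equal in both arms), and 0.05 as a second ICC.

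**All-patient denominator.** Outcome in each arm = r × g. With no difference in control, the spurious difference is (r1 − r0) × g. Effective size per arm is 5265 / (1 + 38 × 0.01) = 5265 / 1.38 = 3815 at ICC 0.01, and 5265 / 2.90 = 1816 at ICC 0.05. The last two columns give the approximate chance of p < 0.05.

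| g | Recorded, control v intervention | Outcome | Difference (points) | OR | ICC 0.01 | ICC 0.05 |
|---|---|---|---|---|---|---|
| 30% | 60% v 65% | 18.0% v 19.5% | 1.5 | 1.10 | 39% | 21% |
| 20% | 60% v 70% | 12.0% v 14.0% | 2.0 | 1.19 | 74% | 43% |
| 30% | 60% v 70% | 18.0% v 21.0% | 3.0 | 1.21 | 91% | 63% |
| 40% | 60% v 70% | 24.0% v 28.0% | 4.0 | 1.23 | 98% | 79% |
| 30% | 60% v 80% | 18.0% v 24.0% | 6.0 | 1.44 | over 99% | 99% |

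**Recorded patients only.** Let 60% be recorded in both arms with 30% controlled. The intervention adds a further 10% of patients, of whom a share x is controlled. The control arm reads 30.0%; the intervention arm reads (0.60 × 0.30 + 0.10 × x) / 0.70.

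- x = 10%: 0.19 / 0.70 = 27.1%, against the intervention.
- x = 30%: 0.21 / 0.70 = 30.0%, no bias.
- x = 50%: 0.23 / 0.70 = 32.9%, in its favour.

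The sign depends on who the extra recorded patients are. The analysed set is defined after randomisation, by something the intervention may change.

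**All registered asthma patients.** Only at-risk patients are flagged. If recording changes only in them and they form a fraction f of all asthma patients, the spurious difference becomes f × (r1 − r0) × g, with g taken in the at-risk patients. The article does not give f, so no size is put on this.

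**Last recorded value.** If that rule covers RCP3Q, a patient not asked during follow-up could carry an answer from before randomisation. This narrows the recording gap, and with it the differences in the table. It also places baseline answers in a follow-up outcome and dilutes any true effect.

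**The case against.** The strongest reply is that the article names a population and a definition, and leaves the treatment of patients without an answer to an analysis plan that is not shown. That is partly right. The article nowhere says that an unrecorded patient counts as not controlled, and silence on missing data would not be a fault in a condensed article. What stands is that the outcome as worded sets a percentage of all patients. Any later rule has to depart from that wording or accept the mixture, and moving to recorded patients brings its own selection.

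A reader might also infer more than the article supports:

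- **That RCP3Qs are recorded only at reviews, and that the intervention triggers more reviews.** The Control section lists the questions as part of recognised management, next to the annual review, and does not confine them to it. Each practice agrees its own response to the flag, and more reviews are not named as a required action. Higher recording is a reasonable expectation from the design, not a stated fact.
- **That the outcome must rise.** It rises on the all-patient denominator if recording rises and some of the extra recorded patients are controlled. On the recorded-only denominator it can move either way or not at all.
- **That the last-recorded-value rule governs this outcome.** That sentence does not name RCP3Q, and its section covers both baseline and outcome data. If it did apply, it would shrink the artefact.
- **That the sizes above apply to all asthma patients.** They are for at-risk patients only.

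It is also fair that the recording and control rates have no source in the article. They show how sensitive the outcome is; they do not predict a result.

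**Conclusion.** The point holds as a weakness in the stated secondary outcome, and it should be corrected. On the literal denominator, a recording gap of 10 percentage points with 20% to 40% control among those recorded produces a spurious 2 to 4 points in at-risk patients. In a trial of this size that would often reach p < 0.05: 74% to 98% of the time at ICC 0.01, and 43% to 79% at ICC 0.05. This rests on assumed rates, on equal control in the two arms, and on recording actually differing by arm, which the design makes plausible but the article does not state. With recorded patients only, the direction cannot be predicted. In all asthma patients any effect would be diluted. The documents do not support saying that the intervention will necessarily inflate this outcome.

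**What to change.** Extraction takes place at the end of the study, so the definition can be fixed beforehand without new data:

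1. Count only RCP3Q answers dated within the 12-month follow-up window, and say whether the last-recorded-value rule applies to them inside that window.
2. Report the proportion of patients with any RCP3Q recorded in the window, by arm, as a process outcome.
3. Present control in three categories: controlled, not controlled, not recorded. Do this separately for at-risk and all registered asthma patients.
4. State that the simple all-patient percentage will not be interpreted as an effect on control.
5. Add, as a sensitivity analysis, multiple imputation or inverse-probability weighting for recording that uses pre-randomisation data. State its assumptions: it needs recording to be explained by the data available, which may not hold here.

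The cost is a few lines of wording, some extra analysis and a more cautious conclusion about control. The primary outcome and sample size stay as they are.

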#### Process evaluation outcomes

The outcomes include quantitative and qualitative assessments of the views of healthcare professionals and patients, practice procedures and processes of care, staff awareness and behaviours, and indicators of uptake, implementation and engagement with the intervention. The process evaluation will also explore how key intermediary and primary and secondary outcomes (e.g. asthma control) are affected by contextual characteristics (e.g. practice characteristics), including identification of factors that will improve effectiveness and sustainability in practice.

#### Safety outcomes

There will be no documentation or reporting of non-serious adverse events. Deaths and hospitalisation are the primary effectiveness outcome and will not be reported as safety measures. Practices will be asked to capture complaints or important study-related adverse events by completing a complaints/adverse events form and forward it to the Norwich Clinical Trials Unit (NCTU).

### Data collection

#### Baseline characteristics and outcome data

All practices expressing interest in the study are asked to complete an initial questionnaire to provide basic data on practice characteristics.

All participating practices must agree to share their practice EHRs with Optimum Patient Care (Cambridge, UK). Obtaining data in this way not only permits linkage to different databases (practice EHRs, Office for National Statistics (ONS), Hospital Episode Statistics (HES)), but also permits data capture without burdening the practice or patients. All practices (control and intervention) are asked to insert a specific Read code that cannot be readily removed by practice staff into the EHRs of at-risk asthma patients to denote inclusion in this study. This will be used by data managers and statisticians to identify these patients and distinguish their data from other patients with active asthma in the practice. For the purposes of data collection, active asthma is defined using the QOF criterion [27]: Read code for asthma diagnosis plus asthma therapy in the past year, excluding those coded as asthma resolved but not excluding QOF exception codes. At the end of the study, data extractions will be obtained for all patients with asthma in the practice containing data for the 12 months before randomisation and the 12 months following the activation of the flag in the intervention practices. The mean time from randomisation to activation of the flag will be calculated for all intervention practices, and data collection will be captured for 12 months from this time after randomisation in the control practices. For clinical event data and for patients’ demographic and other characteristics (weight, height, smoking status, etc.) the last recorded value will be obtained.

#### Health economic data

Resources associated with establishing the at-risk register, training, the CDSS and practice support will be estimated from questionnaires and data obtained from the training website. Additionally, details of patients’ NHS resource use will be extracted from routinely recorded data, where this will include all contacts with health professionals and hospital admissions and asthma-related medications.

#### Process evaluation data

Data captured from the training website for the purpose of process evaluation include module completion rates, time taken to undertake the training, time that the training took place, the number of ‘hits’ on the website resource pages, and changes in knowledge, attitudes and motivation during the training as indicated by self-assessment answers. Likewise, data collected from the helplines and phone calls to practices conducted between 2 and 6 weeks capture details of problems with the intervention and practice engagement. During the second training module, practice teams will be asked to complete online action plans, and these will be captured along with notes from the webinar facilitator, and recordings of webinars to assess details of, and variation in, practice-level dissemination and implementation of the intervention.

After the training, all practice representatives from intervention practices are asked to complete an online questionnaire to provide feedback regarding their experiences and the perceived impact of the training and flags. This will supplement the data captured by the training software and assess the acceptability of the intervention, further changes in knowledge, attitudes and motivation, etc. over time and potential mechanisms by which the training and flags may impact on processes of care. At the end of the study all practice representatives from the intervention practices will be asked to complete a further online questionnaire to provide information regarding their experience of the intervention and its integration into routine practice. ARRISA-UK practice champions from intervention practices and practice contacts from control practices will also be asked questions about major changes in practice asthma management policies over the preceding 12 months.

Taking a sequential, explanatory approach, findings from analyses of preliminary quantitative data will be used to inform sampling and topic guides for focus groups and interviews with relevant stakeholders towards the end of the study. These will explore, in more depth, causal mechanisms, impacts and any unintended consequences of the intervention, the acceptability of the intervention and contextual factors affecting implementation. It is anticipated that dual moderator focus groups [30] or interviews, will be undertaken with representatives from at least six practice/staff group teams (approximately eight participants per focus group) across several study regions. Practice staff and patients at participating practices will be identified and approached via the practice champion. Both patients and practice staff will be consented by process evaluation researchers prior to being involved in focus groups and/or qualitative interviews. A maximum diversity sample of participants will be recruited to reflect a range of engagement with the intervention/training and practice and staff characteristics, guided by quantitative data if this identifies issues for particular staff groups or types of practice. Each focus group will last approximately 1 h and will be digitally audio-recorded, then transcribed verbatim. A further three focus groups, using the same methodology, will be undertaken with patients from three of the practices represented in staff focus groups. The purpose of these focus groups will be to explore patients’ experiences and perspectives on the strengths and limitations of ‘at-risk’ registers and their potential for impact on patients’ asthma management. Fewer focus groups and interviews will be undertaken if data saturation becomes apparent. Information from early focus groups or interviews may also inform refinements to the end-of-study questionnaires used to collect quantitative data on the consequences and integration of the intervention into routine practice from across a broad range of practices.

